## Abstract

**Background:**

About 69% of Americans living with spinal cord injury (SCI) suffer from long-term debilitating neuropathic pain, interfering with the quality of daily life. Neuropathic pain is refractory to many available treatments—some carrying a risk for opioid addiction—highlighting an urgent need for new treatments. In this study, we will test our hypothesis that Spring Forest Qigong™ will reduce SCI-related neuropathic pain by improving body awareness. We will determine whether remotely delivered Qigong is *feasible* and we will collect data on neuropathic pain, and other reported associations with pain such as spasms frequency and/or severity, functional performance, mood, and body awareness.

**Methods:**

In this quasi-experimental pilot clinical trial study, adults with SCI will practice Qigong at home with a 45-min video, at least 3 × /week for 12 weeks. The Qigong practice includes movements with guided breathing and is individualized based on functional abilities, i.e., the participants follow along with the Qigong movements to the level of their ability, with guided breathing, and perform kinesthetic imagery by focusing on the feeling in the whole body as if doing the whole-body Qigong movement while standing. The highest, average, and lowest neuropathic pain ratings perceived in the prior week will be recorded weekly until the 6-week follow-up. The other outcomes will be collected at 5 time points: at baseline, midway during the Qigong intervention (6 weeks), after the Qigong intervention (12 weeks), after a 6-week and 1-year follow-up. Rate parameters for the feasibility markers will be estimated based on the participants who achieved each benchmark.

**Discussion:**

The University of Minnesota (UMN)’s Institutional Review Board (IRB) approved the study (IRB #STUDY00011997). All participants will sign electronic informed consent on the secure UMN REDCap platform. The results will be presented at academic conferences and published in peer-reviewed publications.

**Trial registration:**

ClinicalTrial.gov registration number: NCT04917107, (this protocol paper refers to the substudy), first registered 6/8/2021.

## Introduction

### Background and rationale

About 69% of the 299,000 Americans living with spinal cord injury (SCI) suffer from debilitating neuropathic pain, interfering with general activity, mobility, mood, sleep, and quality of life [1–3]. Yet, neuropathic pain is refractory to many treatments, and some medications carry a risk for opioid addiction, highlighting a need for new treatments [4].

SCI dramatically alters the inflow of sensory information [5–7]. The brain uses a prediction framework in which predictions of sensory input are compared to actual sensory input [5–7]. This disconnect between predicted and actually perceived sensory information leads to altered brain circuitry related to sensory information, including increased pain sensation, which in turn, drives the neuropathic pain perception [5–7].

Concurrently, recent studies showed that SCI-related brain alterations impact body awareness in addition to pain perception [8–11]. Mind and body approaches—known for training body awareness—have been shown to reduce pain in populations with chronic low back pain and fibromyalgia, but evidence of its effectiveness in adults with SCI is limited [12–20]. Adaptive Yoga vs. waitlist group decreased depression and improved self-compassion, but not pain in adults with SCI [19]. A seated Tai Chi program (single-arm study) was well-tolerated in adults with SCI, reduced pain, and improved emotional and physical well-being immediately after each session [20]. However, the weekly in-person classes were associated with a 60% drop-out, and only included adults with paraplegia were included. While these are promising results, more studies are needed.

Qigong—a mind and body approach that incorporates gentle body movements, paired with a focus on breathing and body awareness to promote health and wellness—is accessible for adults with SCI due to the simple, gentle movements, which can be done in a sitting or lying position or by doing kinesthetic imagery of the movements in addition to active movements to the level of their ability [15, 21]. Practicing Qigong has been recognized to improve posture, body awareness, and emotional balance [15]. Some Qigong programs are available online, which helps make the practice accessible for adults with SCI with transportation issues or who live too far away from Qigong centers.

### Objectives

In this quasi-experimental study, we will test our hypothesis that the remotely delivered Qigong will reduce SCI-related neuropathic pain by improving body awareness. If our hypothesis is validated, the outcome of our work will be the first step in demonstrating a potentially effective therapy for adults with SCI-related neuropathic pain. To test this hypothesis, we will determine whether 12 weeks of remote Qigong is *feasible and well-tolerated* and whether it reduces neuropathic pain in adults with SCI. Given the reported associations with pain, we will assess whether Qigong practice reduces spasms frequency and/or severity, and improves function, mood, and body awareness. The feasibility of the 6-week follow-up will investigate how long potential Qigong effects remain without practicing. After the 6 weeks, participants can resume practice at will. The feasibility of the 1-year follow-up will examine possible behavioral changes of participants in practicing Qigong in their daily life.

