## Methods: participants, intervention, and outcomes

### Trial design

The study flow chart of this quasi-experimental pre-post design is presented in Fig. 1. Participants with SCI-related neuropathic pain and with complete or incomplete paraplegia or tetraplegia will perform 12 weeks of “Five Element Qigong Healing Movements” of Spring Forest Qigong™ with an online video at home, at least 3 × /week, 41 min/session. *Individual weekly check-ins* (15–30 min) are organized during the Qigong practice to address questions and demonstrate movements over Zoom if needed. Qualitative information will be collected about their adherence, adverse outcomes if any, perceptions, effects, and satisfaction with the Qigong practice. During the whole study period, we will record weekly the highest, average, and lowest neuropathic pain intensity ratings perceived in the prior week, the dose of neuropathic pain medication, recent illnesses, health care utilization, and/or recent hospitalizations, and any activity that would indicate community integration.

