#### Eligibility criteria

We plan on recruiting 18 adults with SCI-related neuropathic pain, who are 18–75 years old, with SCI of ≥ 1 year, medically stable with complete or incomplete paraplegia (T1 and below) or tetraplegia (C4 and below), and with the highest level of SCI-related neuropathic pain ≥ 3 on the Numeric Pain Rating Scale [22].

We estimate the average age of participants to be 43 years old [23], and the sex ratio to be 4:1 (men:women) [4, 23]. About 24% of SCI occur among non-Hispanic Blacks [4, 23]. Of note, Minnesota has a 79.10% non-Hispanic white population and 7.00% non-Hispanic Blacks [24]. The exclusion criteria are uncontrolled seizure disorder; cognitive or communicative impairments that prevent participants from following directions or learning; ventilator dependency; other major medical complications; treatments for neuropathic pain other than medication.

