### Interventions

#### Explanation for the choice of comparators

Because this is the first study on Qigong in adults with SCI-related neuropathic pain, we decided on a quasi-experimental design and did not include a control group or a sham version of Qigong. We already have shown in a previous study with a similar group of adults with chronic SCI and similar neuropathic pain intensity levels, that neuropathic pain medication-only does not change the neuropathic pain intensity levels or any of the other SCI-related outcomes [25].

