#### Relevant concomitant care permitted or prohibited during the trial

Concurrent practice of other mind–body approaches is not permitted. Their regular standard-of-care (any medication intake) as well as health care appointments will be maintained to ensure adequate care for other SCI-related symptoms, but appointments for neuropathic pain (e.g., osteopathy) will not be scheduled or permitted during the study.

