#### Statistical methods

Rate parameters for the feasibility markers will be estimated based on the participants who achieved each benchmark, with 95% confidence intervals constructed based on exact binomial confidence interval. The continuous measures of feasibility will be summarized using descriptive statistics with 90% confidence intervals constructed. The occurrence of protocol deviation or non-adherence will be summarized and tabulated using frequency tables. The reasons of protocol deviation or non-adherence will be documented and investigated for improved clinical design in future large studies.

All quantitative variables will be summarized using descriptive statistics for all subjects as well as each group at each time point. For longitudinal outcomes, across-time changes and correlations will also be estimated for all participants as well as each group that will be used for sample size determination in future studies. All analyses will be done using standard statistical software including SAS, Stata, and R. The data analysis from this quasi-experimental study will provide an estimate of key trial elements to determine whether to proceed to a larger definitive randomized controlled trial.

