## Discussion

In this quasi-experimental study, we will test our hypothesis that Spring Forest Qigong™’s Five Element Qigong Healing Movements is feasible and will reduce SCI-related neuropathic pain by improving body awareness. To our knowledge, this will be the first study using Qigong for neuropathic pain relief in adults with SCI. Adults with SCI-related neuropathic pain were involved in the design of this study. This study will provide preliminary evidence-based data on the feasibility of remotely delivered Qigong and whether Qigong practice reduces neuropathic pain and pain-related outcomes. The remote delivery of Qigong offers multiple applications for broad use in the home or community, as a stand-alone treatment or in conjunction with other treatments.

There are some limitations to this study. This quasi-experimental study will be conducted on a limited sample size and thus the results will need to be validated in a larger sample size and compared to a control group. The follow-up period with no intervention is 6 weeks. We will collect a 1-year follow-up to evaluate possible behavioral change. The data from the present work will inform the design of future randomized controlled trials with adequate sample size, intervention dosage, and follow-up duration.

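### The protocol promises to test that Qigong reduces pain by improving body awareness, but one uncontrolled group of 18 with descriptive analysis can show neither effect nor mechanism

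*Protocol article*

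**What the plan says.** **The claim.** The Objectives section states that "we will test our hypothesis that the remotely delivered Qigong will reduce SCI-related neuropathic pain by improving body awareness". It goes on to say what follows if the hypothesis is validated, and that the study will determine whether Qigong lowers neuropathic pain. The Abstract (Background) carries the same hypothesis. The Discussion repeats that the programme "is feasible and will reduce SCI-related neuropathic pain by improving body awareness", and promises data on whether the practice lowers pain.

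**The design.** Under Trial design: "The study flow chart of this quasi-experimental pre-post design is presented in Fig. 1". The section on the choice of comparators says the investigators "did not include a control group or a sham version of Qigong". Its reason is a previous study by the same team in a similar population, reported as showing that "neuropathic pain medication-only does not change the neuropathic pain intensity levels or any of the other SCI-related outcomes".

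**The size.** The Sample size section sets 18 participants from expected accrual. It supports this number by interval width: ±21% and ±14% for feasibility rates of 70% and 90%, and ±0.5 for pain. It gives no power or effect size for the pain or mechanism hypothesis.

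**The analysis.** The Statistical methods section says: "All quantitative variables will be summarized using descriptive statistics for all subjects as well as each group at each time point". Changes over time and correlations are also estimated, for use in planning later trials. It describes no mediation analysis and no criterion by which the hypothesis would count as validated.

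**The limitation.** The Discussion says the results will have to be confirmed in a larger sample and against a control group.

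**The concern.** The objective contains two causal statements: Qigong lowers pain, and it does so through body awareness. The first needs some account of what pain would have done without Qigong. The second needs that too, and also a way to separate the path through awareness from other explanations of why pain and awareness move together.

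The plan provides neither. A fall in pain between baseline and week 12 combines any Qigong effect with the passage of time, expectation, and the individual weekly check-ins of 15–30 minutes.

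The Statistical methods section says the results will inform whether to proceed to a definitive randomized trial. If a favourable pre-post change is reported as a validated hypothesis, that decision, and readers of the results, would rest on an effect and a mechanism that were never tested.

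**Working it through.** **1. The plan's own figures.** With N = 18, the normal-approximation half-width is 1.96 × √(p(1−p)/18).
- p = 0.70: 1.96 × √(0.21/18) = 0.212, stated as ±21%.
- p = 0.90: 1.96 × √(0.09/18) = 0.139, stated as ±14%.

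Both reproduce. The ±0.5 for pain implies an SD of 0.5 × √18 / 1.96 = 1.08. The article gives no SD, so this figure cannot be checked. All three figures describe the precision of an estimate in one group. None refers to a contrast with a comparator or to a mediated effect.

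**2. Effect.** Write the mean pre-post change as Δ = τ + β, where τ is the part due to Qigong and β is everything else that happens over the same weeks. One group estimates Δ only, so τ and β cannot be separated. A larger sample narrows the interval around Δ and still does not identify τ. Reading Δ as the Qigong effect requires β = 0. The only support offered for that is the earlier study, which is cited for medication alone. As described, it does not address expectation or weekly contact, and the analysis section gives it no role.

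**3. Mechanism.** The nearest planned quantity is a correlation between changes. Assume, for illustration, an observed correlation of 0.3 (the article gives no value). With Fisher's transformation:
- atanh(0.3) = 0.310.
- N = 18: standard error 1/√15 = 0.258, limits 0.310 ± 0.506, back-transformed to −0.19 and 0.67.
- N = 13 (18 × 0.70 = 12.6, using the 30% attrition given in the retention section): standard error 1/√10 = 0.316, limits 0.310 ± 0.620, back-transformed to −0.30 and 0.73.

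An assumed correlation of 0.5 at N = 18 gives 0.04 to 0.78. That interval excludes zero, yet it still would not show mediation. Less pain may improve awareness, or a third factor may move both. One listed instrument, the Revised Body Awareness Rating Questionnaire, is itself described as measuring how pain or tension affects awareness and function, so some association with pain is to be expected.

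**4. Side by side.**

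| Stated aim | What the design and analysis provide |
|---|---|
| Qigong lowers pain | Mean within-person change in one group |
| It does so by improving awareness | Correlations, estimated for planning |
| Hypothesis may be validated | No criterion stated, descriptive summaries |
| Feasibility and tolerability | Benchmarks and exact intervals: matched |

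Only the last row is matched.

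**5. Could an unseen plan repair this?** An analysis plan could name a model or a main measure. It could not add a comparator. The phrase in Statistical methods about each group does not supply one either: the article defines no groups, and it rules out subgroup analyses.

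**The case against.** **The study is openly preliminary.** The article calls it a pilot, says a positive result would be only a first step, describes the effect estimates as a basis for hypotheses, sets N by accrual rather than power, and names the missing control as a limitation. This stands and softens the point: most of the document already reads as a feasibility study. It does not remove the conflict, because the Objectives and Discussion keep the language of testing and validation.

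**A pre-post study can estimate change.** Agreed. The plan does so, and that estimate is useful. What it cannot do is attribute the change.

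**The design has internal leverage.** Weekly ratings continue through a six-week period without practice, and a return of pain then would be suggestive. But all participants follow the same sequence, the check-ins are also tied to the practice period, and the Objectives use this phase to see how long effects last.

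**Stronger readings a reader might infer, which the documents do not support:**
- *That pain medication may change freely.* The concomitant-care section says "Their regular standard-of-care (any medication intake) as well as health care appointments will be maintained". That can mean continued or held constant. Dose is recorded weekly, appointments for neuropathic pain and other mind-body practice are barred, and non-drug pain treatments are an exclusion.
- *That the three pain ratings and several awareness scales inflate the false-positive rate by a calculable amount.* The plan specifies no tests and no screen of pairings, so there is no error rate to calculate. Ranking exploratory measures can be left to an analysis plan.
- *That entry "with the highest level of SCI-related neuropathic pain" at or above 3 produces a known regression to the mean.* The direction is plausible for that rating, but the article gives no mean, SD or reliability, so no size can be established.

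**Conclusion.** The point holds as a mismatch between the stated objective and the design with its analysis. The study can deliver feasibility rates and within-person change with intervals. It cannot deliver a conclusion that Qigong reduces pain, or that body awareness is the route.

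The mismatch rests on the article's own statements (one group, no control or sham, descriptive analysis) and on no assumed value. The correlation intervals in the working are illustrations on assumed correlations of 0.3 and 0.5. The sample size needs no correction on this ground, since the article makes no power claim for pain or mechanism.

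The change should be made because it alters what may be concluded. It is a matter of wording, and it does not mean the pilot is unsound for its feasibility purpose.

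**What to change.** **Reword the Abstract (Background), Objectives and Discussion.** State that the study will estimate feasibility and tolerability, and will describe within-person change in neuropathic pain and body awareness with confidence intervals. Any correlation between the two changes is hypothesis-generating, and no conclusion will be drawn on effect or mechanism. Remove the wording about testing the hypothesis, about its being validated, and about determining whether Qigong reduces pain. Treat the parallel wording on spasms, function and mood in the same way. Since the article expects no further protocol changes, carry the reworded aim into the analysis plan and the results report as well.

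**Optional.** Tabulate the neuropathic-pain medication dose, already recorded weekly, beside the pain change, as description only. Do not exclude participants whose dose changed: that would condition on something that happens after baseline and may respond to pain, and it would shrink an already small sample. This asks for reporting of collected data and proposes no clinical rule.

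**Cost.** A less ambitious claim, some edited sentences and at most one extra table. No new data, visits or participants are needed.

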## Methods: participants, intervention, and outcomes

### Trial design

The study flow chart of this quasi-experimental pre-post design is presented in Fig. 1. Participants with SCI-related neuropathic pain and with complete or incomplete paraplegia or tetraplegia will perform 12 weeks of “Five Element Qigong Healing Movements” of Spring Forest Qigong™ with an online video at home, at least 3 × /week, 41 min/session. *Individual weekly check-ins* (15–30 min) are organized during the Qigong practice to address questions and demonstrate movements over Zoom if needed. Qualitative information will be collected about their adherence, adverse outcomes if any, perceptions, effects, and satisfaction with the Qigong practice. During the whole study period, we will record weekly the highest, average, and lowest neuropathic pain intensity ratings perceived in the prior week, the dose of neuropathic pain medication, recent illnesses, health care utilization, and/or recent hospitalizations, and any activity that would indicate community integration.

**Fig. 1 Fig1:**
[figure not shown]
Study flow chart

The outcomes associated with pain will be collected at 5 time points: at baseline, midway during the Qigong intervention (6 weeks), after the Qigong intervention (12 weeks), and after the 6-week and 1-year follow-up. During the 6-week follow-up, participants will not practice Qigong but receive regular standard of care as needed. After the 6 weeks, the participants can restart their Qigong practice at the frequency of their choice so we can evaluate any change in behavior occurring when no instructions are given. Participants will receive $100 upon study completion, through a Greenphire ClinCard. The Qigong introduction class and video access will be paid for by the study.

#### Study setting

Since this is a remote-only study, participants practice at home or in any location of their choice with a Wi-Fi connection.

#### Eligibility criteria

We plan on recruiting 18 adults with SCI-related neuropathic pain, who are 18–75 years old, with SCI of ≥ 1 year, medically stable with complete or incomplete paraplegia (T1 and below) or tetraplegia (C4 and below), and with the highest level of SCI-related neuropathic pain ≥ 3 on the Numeric Pain Rating Scale [22].

We estimate the average age of participants to be 43 years old [23], and the sex ratio to be 4:1 (men:women) [4, 23]. About 24% of SCI occur among non-Hispanic Blacks [4, 23]. Of note, Minnesota has a 79.10% non-Hispanic white population and 7.00% non-Hispanic Blacks [24]. The exclusion criteria are uncontrolled seizure disorder; cognitive or communicative impairments that prevent participants from following directions or learning; ventilator dependency; other major medical complications; treatments for neuropathic pain other than medication.

#### Recruitment

Participants will be recruited in outpatient locations within the newly funded Spinal Cord Injury Model System Center (Minnesota Regional Spinal Cord Injury Model System) and the community. Specifically, we have collaborators within the Minneapolis VA Health Care System including the Minnesota Paralyzed Veterans; M Health Fairview (Minneapolis); MN SCI associations; Regions Hospital; Courage Kenny Rehabilitation Institute; Get Up Stand Up To Cure Paralysis; Unite2fight paralysis, and Fit4Recovery.

Since this is a remote-only study, we can recruit nationwide. We will use volunteer sampling through fliers, and post study-relevant information on social media and relevant websites. We will also use convenience sampling by having the health care providers in hospitals and organizations provide enrollment information and materials to potential participants.

Given that this is a quasi-experimental design, the following topics are not applicable: Assignment of interventions: allocation; Sequence generation; Concealment mechanisms; Implementation; Blinding; Who will be blinded; Procedure for unblinding if needed.

